### Baseline characteristics

For the entire group of women recruited, the mean (SD) age was 25.6 (6.1) years; stage of pregnancy was 20.2 (10.7) weeks. The majority or 65.1% of the women had other children and 42.0% of these mothers had a child who had previously had a tooth extracted. The women's mean (SD) score out of 5 for the knowledge questions was 3.0 (1.3). As far as oral health behaviours, 92.3% of mothers brushed their teeth with toothpaste at least once a day and 72.7% of mothers had been to a dentist within the last two years.

### Treatment group comparisons at baseline

Randomization checks were conducted on possible demographic and behavioral differences between groups (Table 1). The distributions of most variables was very similar for the two randomized groups of mothers (specifically, for age, knowledge score, other children, toothbrushing, and seeing the dentist in the prior two years). However, despite the random assignment of communities to treatment conditions, group differences existed for stage of pregnancy and prior tooth extractions for other children in the family. Mothers in the test or MI communities had later stages of pregnancy than mothers in control communities (22.4 vs. 17.7 weeks), and mothers with other children in the MI communities were less likely to have had another child with a tooth extraction (34 vs. 49%). Testing of differences between randomized groups on baseline variables is not particularly informative, because any differences found must by definition be type I errors. However, such tests were performed here for illustrative purposes. Note that the difference in pregnancy stage did reach statistical significance (Z-statistic larger than 2 corresponds to a p-value < 0.05), whereas the difference in tooth extraction prevalence did not. These results illustrate that a difference that could be deemed clinically important may result even within the range of normal sampling variability in the cluster-randomized setting. In contrast, such a difference might be less likely to occur in an individual-randomized design with the same number of participants. Statistical significance aside, what matters is that the group differences (particularly for tooth extraction) may be large enough to be associated with clinically meaningful differences in health outcomes at follow-up in the enrolled children. Therefore, secondary analyses of outcomes will be done with regression adjustment to control differences in stage of pregnancy and presence of other children with tooth extractions as covariates. An unadjusted analysis will be performed as the primary analysis; the results of the adjusted and unadjusted analyses will be compared to determine the impact of the baseline group differences on the results.

**Table 1 T1:** Randomization effectiveness: baseline characteristics of study sample mothers by treatment group.

Variable	N	Test	N	Control	Z^1^
Age (years)^2^	130	25.5 (6.4), 15 - 44	137	25.6 (5.8), 15 - 39	-0.11
Stage of pregnancy (weeks)^2^	102	22.4 (8.7), 6 - 38	90	17.7 (12.1), 0 - 36	2.25
Knowledge score^2^	127	3.1 (1.2), 0 - 5	140	2.9 (1.4), 0 - 5	0.57
Has other children^2^	129	83 (64.3%)	140	92 (65.7%)	0.32
Other child had prior tooth extraction^3,4^	82	28 (34.1%)	92	45 (48.9%)	1.09
Brush with fluoride toothpaste^3^	130	120 (92.3%)	141	130 (92.2%)	0.04
Saw dentist < 2 years ago^3^	130	93 (71.5%)	141	104 (73.8%)	-0.42

^1^Z = observed Z-statistic for comparison of MI and Control groups using Generalized Estimating Equations to account for clustering of subjects within communities

^2^Results shown are mean (SD), minimum - maximum

^3^Results shown are number positive for the variable (% positive).

^4 ^Only responses of mothers with other children are included

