### Inclusion/exclusion criteria

Over a period of about 2 1/2 years, all women in the 9 Cree communities who recently had given birth or were between about the 12^th ^and 34^th ^week of their pregnancy were asked to participate in the study. Any woman knowing of an impending, permanent move out of her community was excluded. Even children born with a medical concern or a congenital anomaly, for example cleft palate were included, if that was the family's wish. Information about the health of the child will be gathered at the outcomes assessment and will be managed in the statistical analysis.

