### Statistical analysis

#### Primary statistical analysis

The primary statistical analysis will be a comparison of caries prevalence in intervention and control groups, using a permutation test[28] with test statistic equal to the difference between caries prevalences in the two groups. A significance level will be determined using the exact permutation distribution of the test statistic, which will be computed by enumerating all possible random assignments of villages to intervention or control conditions according to the randomization scheme. The use of the permutation test accounts for intra-class correlation between outcomes on children in the same village and also addresses concerns over the small-sample performance of statistical methods such as Generalized Estimating Equations [29], which rely on asymptotic theory. An exact confidence interval for the treatment effect (difference in caries prevalences) will be computed using the usual procedure for inverting the permutation test. Peterson et al provide an illustration of the application of this procedure to a group-randomized trial [30]. Additional analyses will be conducted using the same procedures for boys and girls separately.

The main analysis will be done at the end of the study when data collection at 30+/-3 months is complete. No interim analyses will be performed because it is considered extremely unlikely for there to be evidence of a treatment effect prior to collection of the final outcome data on the entire sample. However, a preliminary frequency analysis of the baseline data was done to help the investigators develop an understanding of the characteristics of the sample.

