### Progress of recruitment and power

Two hundred and seventy-two mothers (131 test; 141 control) have been recruited over 2 1/2 years. Because of the cluster-randomized design of the trial, the power of the trial can be determined not only by the total sample size but also by the number of communities and by having sufficient numbers of subjects recruited in each of the communities. Whereas the original projected sample size of 309 women would have yielded 82% power to detect a 20% reduction in caries prevalence from 0.86 to 0.69, power calculations using the actual sample sizes show that the power will be 79% to detect this treatment effect. These calculations assume a loss to follow-up of 5% per year. If we are able to maintain an attrition fraction of 4% per year, the power will be 80%. Power will be very high (> 90%) to detect a 25% reduction in caries prevalence.

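### Stage of pregnancy, a named covariate for the adjusted analysis, is recorded for only 192 of 272 mothers (78% test, 64% control) and has no meaning for those enrolled after birth

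*Protocol article*

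**What the plan says.** All places are in the protocol article.

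- **Treatment group comparisons at baseline.** The primary analysis is unadjusted. Secondary analyses use "regression adjustment to control differences in stage of pregnancy and presence of other children with tooth extractions as covariates", and the two sets of results are to be compared to see what the baseline imbalances do to the findings.
- **Inclusion/exclusion criteria.** The women approached were those who "recently had given birth or were between about the 12^th ^and 34^th ^week of their pregnancy". The Discussion confirms that mothers of newborns were recruited, as a change from the proposal.
- **Progress of recruitment and power.** "Two hundred and seventy-two mothers (131 test; 141 control) have been recruited over 2 1/2 years".
- **Table 1, stage of pregnancy.** Test: N = 102, mean 22.4, SD 8.7, range 6 to 38. Control: N = 90, mean 17.7, SD 12.1, range 0 to 36. Z = 2.25, from Generalized Estimating Equations (GEE) clustered on community. The text adds: "Note that the difference in pregnancy stage did reach statistical significance".
- **Table 1, extraction in another child.** 28 of 82 test and 45 of 92 control. The footnote says "Only responses of mothers with other children are included".
- **Baseline characteristics.** In a sentence introduced as covering all recruited women, "stage of pregnancy was 20.2 (10.7) weeks".
- **Primary statistical analysis.** The permutation test is chosen partly because of "concerns over the small-sample performance of statistical methods such as Generalized Estimating Equations".

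**The concern.** Comparing an adjusted with an unadjusted estimate isolates the effect of adjustment only if both come from the same children. A covariate that cannot be defined for part of the enrolled sample breaks this. Either those mothers leave the adjusted model, or they enter it with an arbitrary code. In the first case a shift in the estimate may be selection. In the second, a code of 0 weeks would treat the latest enrollers as the earliest.

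The 0-week minimum in the control arm raises the question whether such a code is already in Table 1. If it is, the stage-of-pregnancy imbalance reported in the abstract and the baseline section may be partly or wholly a matter of coding.

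**Working it through.** **1. Reproduce the plan's overall figure.** Pooled mean from Table 1: (102 × 22.4 + 90 × 17.7) / 192 = 3877.8 / 192 = 20.2. Pooled SD: √{[101 × 8.7² + 89 × 12.1² + 102 × (22.4 − 20.197)² + 90 × (17.7 − 20.197)²] / 191} = √(21731 / 191) = 10.7. This matches 20.2 (10.7), so the figure given for all recruited women rests on 192 of them.

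**2. Mothers without a stage value.**

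| | Recruited | With value | Without |
|---|---|---|---|
| Test | 131 | 102 (77.9%) | 29 (22.1%) |
| Control | 141 | 90 (63.8%) | 51 (36.2%) |
| All | 272 | 192 (70.6%) | 80 (29.4%) |

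**3. The extraction covariate.** The Table 1 row covers 82 + 92 = 174 of 272 and so omits 98 (36.0%). Mothers with no other child number (129 − 83) + (140 − 92) = 46 + 48 = 94. For them the answer to whether another child has had an extraction is no. That leaves 98 − 94 = 4 (1.5%) without a value: 3 test (131 − 128) and 1 control (141 − 140). On this coding the contrast is 28/128 = 21.9% against 45/140 = 32.1%, rather than 34.1% against 48.9% among mothers with other children.

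**4. Is the control distribution plausible as plain gestational weeks?** For a single-peaked distribution on 0 to b with mean μ below b/2, the largest variance is 2bμ/3 − μ². With b = 36 and μ = 17.7 this is 424.8 − 313.3 = 111.5, an SD of 10.6. The reported SD is 12.1. The values therefore seem to cluster in more than one place.

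**5. Would zeros explain it?** Suppose a fraction f of control values are 0 and the rest have the test-arm mean and SD.
- Matching the mean: f = 1 − 17.7/22.4 = 0.210, or 18.9 of 90.
- Implied SD: √[0.790 × 8.7² + 0.210 × 0.790 × 22.4²] = 12.0, against 12.1 reported.

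The reverse check removes k zeros from the reported control values:

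| k | Remaining mean | Remaining SD | Test minus control (weeks) |
|---|---|---|---|
| 0 | 17.7 | 12.1 | 4.7 |
| 1 | 17.9 | 12.0 | 4.5 |
| 10 | 19.9 | 11.0 | 2.5 |
| 19 | 22.4 | 8.9 | 0.0 |
| 20 | 22.8 | 8.5 | −0.4 |

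With 19 zeros removed, the control arm looks like the test arm (22.4, SD 8.7). With fewer, part of the imbalance remains.

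**6. The significance statement.** Z = 2.25 gives two-sided p = 0.024 on the normal reference. On a t reference with 9 − 2 = 7 df (an assumption), p = 0.059; the 5% critical value is 2.36.

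**The case against.** **Missing-data handling belongs in the full plan.** The article does not say that mothers without a value are dropped, and such detail is commonly left out of an article. This stands as far as it goes, and the loss of 29% is therefore conditional. But the article itself fixes the covariate and the purpose of the comparison, and no handling rule gives a gestational week to a mother who has already delivered.

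**A reader might infer that both covariates are missing on a large scale.** The documents do not support this for extraction. The restriction in Table 1 is a display choice, and step 3 leaves 4 mothers without a value.

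**A reader might infer that the imbalance is a coding artefact.** The documents give neither the coding of post-birth mothers nor the number of zeros. Step 5 chooses f to match the mean, so only the SD agreement is a check, and it assumes that the other controls resemble the test arm. Genuine clusters of early and late enrolment could also give a large SD. The 12-week limit is approximate, and the test arm has values of 6 and 38. Nor do the documents say that the 80 mothers without a value are those enrolled after birth. This objection stands: the pattern justifies a data query and no more.

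**A reader might infer that the plan rejects GEE and then relies on it.** It voices concern about GEE when choosing the primary test. It calls the baseline tests illustrative and selects covariates on possible clinical importance; extraction was selected with Z = 1.09. The p-value of 0.024 or 0.059 therefore changes no planned analysis.

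**Conclusion.** The point holds for one covariate in a secondary analysis. Stage of pregnancy is available for 70.6% of mothers, with absence of 22.1% in the test arm and 36.2% in the control arm, and it is undefined after birth. If mothers without a value are excluded, the planned adjusted-versus-unadjusted comparison mixes adjustment with selection and cannot serve its stated purpose.

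The 0-week minimum and the SD of 12.1 suggest, but do not prove, that some post-birth controls were coded 0. About 19 such records could account for the whole 4.7-week difference, under the assumption that the other controls resemble the test arm.

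The wording that the stage difference reached significance depends on a normal reference with 9 communities and does not hold on t with 7 df. This is a reporting correction only. The unadjusted primary permutation test is not affected by any of this.

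**What to change.** 1. Check the 0-week control records, and any other values outside the recruitment window, against enrolment and birth dates. If post-birth mothers were coded 0, correct Table 1, the overall mean and the imbalance statements in the abstract and baseline section. In any case, state that the overall mean rests on 192 mothers.
2. Replace stage of pregnancy by signed weeks from enrolment to the child's birth, negative if enrolled after birth. Birth dates must be held, since the outcome examination and the control mailings are timed by the child's age; enrolment dates are assumed to be on file. One small drawback is that for pregnant women the birth date falls after enrolment, so the variable is not purely a baseline measure.
3. Define the extraction covariate for all mothers, preferably in three levels: no other child, other child without extraction, other child with extraction.
4. Run the adjusted and unadjusted analyses on the same children for the comparison.
5. State that the stage Z of 2.25 comes from GEE with 9 communities, with p about 0.06 on an assumed t reference with 7 df. Alternatively, replace it with a permutation p-value over the 2 × 35 = 70 assignments that the randomization scheme allows.

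The cost is a record check, recoding of data the trial should already hold, a re-run of Table 1 and a few sentences. No new data collection is needed, and the primary analysis does not change.

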## Discussion

This project with Aboriginal mothers aimed to evaluate the effectiveness of a specific behavioural intervention, Motivational Interviewing, to decrease the prevalence of early childhood caries in their children. The location of the trial in remote communities in northern Canada added to the project's challenges.

### Community consultation

The process of community consultation was one of several complex issues that arose during the planning of the trial. Prior to undertaking the trial, extensive discussions throughout the community were undertaken. While disturbances in the balance between bacteria, substrate and host are the local factors associated with ECC, health determinant like economics, social norms and housing conditions also have a substantial impact on the development of the disease [31]. Therefore, any intervention had to be planned with early and continuous community collaboration and consultation and needed to be sensitive to existing beliefs and traditions about parenting practices, child comforting and infant health. Oral health intervention strategies must be sensitive to the intended target population because of the important role that culture plays in shaping health-related attitudes and behaviours in Aboriginal communities [32]. The project investigators, one of whom was the public health dentist for the territory, undertook two years of consultation with community leaders, health care workers and families from Eeyou Istchee to discuss appropriate strategies prior to beginning the trial. In addition, the Research Committee of the CBHSSJB collaborated on this project from its conception.

When the project began, relatively few community-based initiatives to improve the oral health of young children had been undertaken [25,33] and scant few had been conducted as randomized controlled trials [34,35]. The concept, advantages and disadvantages of a randomized controlled trial were discussed at length to ensure that communities understood that, during the trial, "test" communities were to have a more intensive program than "control" communities. The consensus from the consultation was that, since no infant oral health promotion program was currently in place, it was acceptable to participate in a trial to definitively determine the most effective approach.

### Existing organizational structure

Another matter that arose during the planning of the trial was how the project was to articulate with the structure and organization of health care services within Eeyou Istchee. Surveillance, promotion, prevention, protection, regulation, research and training relating to the health of the Cree population in Eeyou Istchee are managed by the Public Health Department of the CBHSSJB. The Department's long-term goal related to this specific project was that, if successful, the MI approach would become a component of the Department's health promotion activities. To that end, their inclination was for the day-to-day work of the project to be undertaken by existing Health Department staff rather than new staff, the so-called "Dental Health Representatives" (DHRs), who were to be specific to the research project. After considerable deliberation, it was decided that existing department staff, women currently employed as Community Health Representatives (CHRs) would do the recruiting of mothers and be the project interveners. The Project Manager who was hired was a dental hygienist from the Cree nation who was born, raised and had worked for several years in Eeyou Istchee.

### Training of project staff and the MI intervention

One of the first steps in launching the project was staff engagement ("buy-in") and training. Because of the decision to engage existing staff (CHRs) as recruiters and interveners in the project, job-postings and hiring did not slow down the start of the project. However, 3 of the 9 communities did not have a CHR on staff at the project's start; therefore, local women (as per the original proposal) were hired to begin recruitment. From the beginning of the project and throughout, the Project Manager visited the communities and met with the project's staff to problem-solve challenges and review procedures. She also maintained regular telephone contact with the staff in each community who were working on the project.

As detailed in the proposal for the trial, a two-day training workshop for CHRs in the 5 intervention or "test" communities was held within the first year of the project. The project's MI consultant provided a template for the MI script and menu that would be used in the counseling sessions with the mothers. By engaging the CHRs in discussion and critique, both the script and the menus were extensively modified to suit the language and style of the Cree. Following the workshop, the menus were finalized, printed on flipcharts and sent with explanatory notes to each CHR in each of the test communities. The MI consultant followed up some months later with an "MI-coaching conference call" to problem-solve MI with the CHRs. A second follow-up workshop was held the next year. Following this workshop, the PM visited each of the communities individually to problem-solve recruiting and MI challenges.

The MI scripts were based on the work of Weinstein[36] and on scripts developed for a previous trial [21,37,38] One script was created for pregnant and new mothers (Additional file 1) and another slightly modified script was developed for mothers after their infant's first tooth had erupted until their child was about 2-years of age. Mothers of newborn, pre-dentate infants were recruited to the trial in addition to pregnant women; this was a variation from the original proposal but was done to ensure that every newborn infant and mother had the opportunity to participate. An important aspect of improving infant oral health is enhancing the oral health of the mother to prevent transmission of cavity-causing bacteria from mother to infant. With this in mind, pregnant and new mothers were given "privilege cards" that allowed them expedited dental services at their community's dental clinic.

For a variety of reasons, CHRs in many of the communities were challenged by the process of subject recruitment and delivering the intervention. The negative side of engaging these existing personnel in a research project was their sense of being overworked and not sufficiently rewarded for this addition to their daily workload. This project was yet another burden for the already busy and in-demand CHRs. Furthermore, the CHRs may have found that expectant women and new mothers were too busy to spend an additional amount of time completing project documents or were simply not interested in participating in a research project. Even though the project investigators had tried to be diligent in following recommended principles of involving Aboriginal communities in research, recruitment of participants was a struggle. Thus, in 2 of the 5 test communities and in 2 of the 4 control communities, recruitment and, for the test communities, delivery of the intervention was eventually completed by the Project Manager. One of the project-specific DHRs achieved success in one test-community and eventually took over the work of a retiring CHR in another test-community. A CHR, aided by the Project Manager, completed and continued the project's work in the 5^th ^test community. Local women who were not CHRs completed recruitment in the remaining 2 control-communities. Recruitment was closed after 2 1/2 years when the number of mothers recruited, though short of the original goal, was sufficient to maintain the power of the trial.

Administrators may request that in order for research trials to be implemented within their organization, existing personnel should work on the project. However, these individuals may simply not have the time, the interest or the desire to participate, despite the provision of extensive in-service training and ongoing support. Therefore, it can be concluded that in these instances, the trial's human and financial resources need to be efficiently and quickly redistributed to ensure success of the project. Despite the initial and ongoing challenges involved with implementing this clinical trial, the results will enhance our understanding of the details of implementation of randomized trials in remote communities. In addition, the role of a client-centred, directive counseling style like Motivational Interviewing in enhancing positive oral health behaviours in Aboriginal families will be better understood.
